### Statistical analyses

The statistical analyses will begin with descriptive analyses of baseline characteristics (age, sex, disease duration, EDSS, other physiologic parameters at baseline and over time, medications, etc.), by treatment allocation ((1) EX + CR, (2) EX + CR-S (3) EX-S + CR or (4) EX-S + CR-S). Continuous variables will be summarized using the statistics mean, median, SD, minimum and maximum. Categorical variables will be summarized with frequency counts and percentages. During the trial, drop-outs and losses to follow-up will be compared between groups to ensure high follow-up rates and comparability and that no particular demographic or site is differentially dropping out of one treatment group. The currently supported version of SAS software will be used to perform all data analyses.

Summary tables will indicate the number of subjects with complete data for each measurement, event or outcome. All analyses will be based on available data, unless otherwise stated, and the intent-to-treat principle. Secondary analyses will examine the per protocol analysis population. All confidence intervals will be two-sided and will use 95% confidence levels. Any analyses requiring significance testing will use a two-sided test at the 5% significance level, unless otherwise specified.

Differences in baseline characteristics between groups will be examined in continuous variables, such as age and disease duration using an ANOVA and categorical variables using a Chi-square tests of association. Informative censoring will be examined with potentially biased imputation and non-informative censoring as well as missing-at random assumptions using multiple imputation to provide sensitivity analyses of the primary results.

The primary analysis will utilize an ANOVA and include an interaction term for the combined treatments. A priori contrasts (stated above in the hypothesis section) will be conducted if the overall test of differences amongst the treatment groups achieves statistical significance. For the pairwise comparisons Dunnett’s test will be used to preserve the Type I error rate. Additional analyses will be conducted as sensitivity analyses using Analysis of Covariance (ANCOVA). These will include site, gender, age and other covariates that may be seen to differ amongst the groups at baseline. Multiple imputation will be used to assess the sensitivity of the primary results to dropouts.

Secondary outcomes will be similarly assessed using ANOVA and ANCOVA procedures and, repeated measures mixed models will be used for measurements that are taken between baseline and 12 weeks.

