## Abstract

**Background:**

Cognitive dysfunction affects up to 70% of people with progressive MS (PMS). It can exert a deleterious effect on activities of daily living, employment and relationships. Preliminary evidence suggests that performance can improve with cognitive rehabilitation (CR) and aerobic exercise (EX), but existing data are predominantly from people with relapsing-remitting MS without cognitive impairment. There is therefore a need to investigate whether this is also the case in people with progressive forms of the disease who have objectively identified cognitive impairment. It is hypothesized that CR and EX are effective treatments for people with PMS who have cognitive impairment, in particular processing speed (PS) deficits, and that a combination of these two treatments is more effective than each individual treatment given alone. We further hypothesize that improvements in PS will be associated with modifications of functional and/or structural plasticity within specific brain networks/regions involved in PS measured with advanced MRI techniques.

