
We propose to treat four groups of participants as noted above. We estimated our sample size using a standard 1-factor analysis of variance approach with a Type I error set at 5%. We computed the sample size necessary to achieve 80% power for such a design assuming conservative changes. For simplicity we used 4 points for the combined treatments, *assuming* that we want to demonstrate a clinically meaningful difference on average and that the two interventions are additive; 4 more correct answers has been suggested by the FDA as a meaningful change [37]*.* We also assumed a change of 2 answers for each of the single interventions and 0 for the sham group [83]. (Note *again* that the learning curve and practice effects will contribute equally to each group and the results shown below are the same if we had chosen 6, 4, 4, 2 *or* other combinations with the same relative spread to accommodate the practice effects, etc.)

Table 6 shows that with 90 participants per treatment group at the time of analysis, there is over 80% power to detect differences as specified (4,2,2,0) across the four groups when the standard deviation of the change is 8 points and the overall Type I error to detect any mean differences is 0.05.

**Table 6 Tab6:** Power for 4 group Analysis of Variance with mean changes in the SDMT of 4 more correct for the combined group; 2 more correct for each of the single intervention groups and 0 change for the Sham Group

**Power**	**n**	**Total N**
0.52751	50.00	200
0.57247	55.00	220
0.61476	60.00	240
0.65423	65.00	260
0.69081	70.00	280
0.72449	75.00	300
0.75533	80.00	320
0.78341	85.00	340
0.80885	90.00	360
0.83179	95.00	380
0.85239	100.00	400

In order to assess the sensitivity of these calculations to assumptions, we conducted a few additional patterns of response and standard deviations. Clearly for any standard deviation smaller than 8, we have more power. For example, if the standard deviation of the change were 7 instead of 8, the power is 91% with 90 patients per group and 81% with 70 per treatment group. If the treatment difference pattern is 4,1,1,0; the power is 86% with four groups assuming a standard deviation of 8.

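### The omnibus gate costs Dunnett's test power without need, and no single Dunnett set covers both single-versus-sham and combined-versus-single comparisons

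*Protocol article*

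**What the plan says.** All places are in the protocol article.

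- **Abstract, Background:** CR and EX are each hypothesised to be effective, and "a combination of these two treatments is more effective than each individual treatment given alone".
- **Aim, design and setting of the study:** there are two primary aims. The first is synergy of CR and EX on processing speed; the second is the individual effect of each.
- **Statistical analyses:** the primary analysis is an ANOVA with an interaction term. The contrasts are introduced as "A priori contrasts (stated above in the hypothesis section") and "will be conducted if the overall test of differences amongst the treatment groups achieves statistical significance". For pairwise comparisons, Dunnett's "test will be used to preserve the Type I error rate". No reference arm is named. Significance tests in general "will use a two-sided test at the 5% significance level, unless otherwise specified".
- **Power analysis:** "We estimated our sample size using a standard 1-factor analysis of variance approach with a Type I error set at 5"%. With 90 per group and an SD of change of 8, "there is over 80% power to detect differences as specified (4,2,2,0) across the four groups", where "the overall Type I error to detect any mean differences is 0.05".

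**The concern.** Two features of the testing plan do not fit the questions it has to answer.

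First, Dunnett's test compares several arms with one reference arm. The stated hypotheses need two references: double sham for the single treatments, and the combined arm for its advantage over each single treatment. Whichever reference is chosen, one group of comparisons falls outside the only multiplicity method named.

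Second, Dunnett's test controls its own familywise error. Requiring a significant omnibus F first cannot make it more valid; it can only remove rejections. At stake are a real effect of the combination over sham that goes undeclared, and a claim that combined treatment beats one treatment alone made without a stated error rate.

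**Working it through.** **Inputs** (Power analysis): 90 per arm at analysis, SD of change 8, mean changes 4,2,2,0 for combined, the two singles and double sham, two-sided 5%. Error df = 360 − 4 = 356. Equal arms, normal data and a common SD are assumed. Dunnett, gated and max-t figures come from simulations of 1,000,000 trials; repeat runs agree to about 0.1 percentage point.

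**1. The plan's own figure.** The mean of 4,2,2,0 is 2, so the sum of squared deviations is 4 + 0 + 0 + 4 = 8. The noncentrality is 90 × 8 / 64 = 11.25. A noncentral F on 3 and 356 df gives power 0.80885, as in Table 6. All 11 rows of that table reproduce.

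**2. Which comparisons one Dunnett set covers.**

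| Comparison | Sham as reference | Combined as reference |
|---|---|---|
| Combined vs sham | yes | yes |
| CR vs sham, EX vs sham (aim 2) | yes | no |
| Combined vs CR, combined vs EX (Abstract hypothesis) | no | yes |

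**3. Can the interaction replace combined versus single?** Under 4,2,2,0 the interaction is 4 − 2 − 2 + 0 = 0, so its test rejects at the 5% alpha level only. Yet the combined arm is 4 − 2 = 2 points better than each single. These are different questions. The standard error of a pairwise difference is 8 × √(2/90) = 1.193. A difference of 2 therefore has noncentrality 2 / 1.193 = 1.68, and power 38.7% unadjusted.

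**4. What the gate does to Dunnett.** The Dunnett critical value for three comparisons is 2.36 and the omnibus critical F is 2.63. A contrast contributes t²/3 to F, so t = 2.36 contributes 2.36² / 3 = 1.86, short of 2.63. A contrast opens the gate by itself only at t = √(3 × 2.63) = 2.81. Dunnett findings between 2.36 and 2.81 can therefore be blocked.

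| Quantity | Dunnett, no gate | Dunnett with gate |
|---|---|---|
| Combined vs sham, 4,2,2,0 | about 84% | 78.6% |
| Each single vs sham, 4,2,2,0 | 24.9% | 24.6% |
| At least one rejection, 4,2,2,0 | 85.5% | 79.6% |
| Combined vs sham, 3,2,1,0 | about 56% | 50.4% |
| Familywise error, all means equal | 5.0% | 3.1% |

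The share of trials in which Dunnett finds something and the gate blocks it is 85.5% − 79.6% = 5.9%.

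**5. What the gate does for contrasts outside Dunnett.** If all five comparisons were run unadjusted with all means equal, the gate would bring familywise error from 18.1% to 4.9%. If instead both singles work as well as the combination (4,4,4,0), the gate is nearly always open and two unadjusted combined-versus-single tests have about 9.0% error. That is weak control: it holds under the complete null and not under this partial null.

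**6. One simultaneous family of all five comparisons, no gate.** The max-t critical value is 2.53.

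| Combined vs sham | As written (gated Dunnett) | Five-contrast max-t |
|---|---|---|
| 4,2,2,0 | 78.6% | 79.5% |
| 4,1,1,0 | 80.7% | 79.4% |
| 3,2,1,0 | 50.4% | 49.5% |

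Under 4,2,2,0 each of the other four comparisons has about 20% power. The max-t entries for 4,1,1,0 and 4,2,2,0 differ only by simulation noise, since the difference is 4 in both.

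**The case against.** **Both primary aims are covered.** A reader might infer that the plan cannot test its primary aims. The document does not support that. Aim 1 is synergy, and the ANOVA carries an interaction term that tests it. Aim 2 is the individual effects, and Dunnett against double sham tests those. What lacks a place beside them is the combined-versus-single hypothesis, which is stated in the Abstract and not listed as a primary aim. This objection stands and sets the limit of the point.

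**The gate does protect error.** A reader might say that it protects nothing. It is unnecessary for a single Dunnett set, but under the complete null it would bring two Dunnett sets (sham and combined as references) from 7.6% to 4.4%. It also matches the test on which the sample size rests. This stands in part: the protection is real but weak, and Dunnett against sham does not need it.

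**The 9% is not the plan's error rate.** The article nowhere says that combined-versus-single tests run unadjusted, and they are pairwise comparisons, for which it names Dunnett. This stands, so the 9% is conditional. At the Dunnett critical value the same two tests have about 3.5% error under 4,4,4,0.

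**Condensation.** The hypothesis section that the text points to is not in the article, but a contrast list and a reference arm are commonly left to the full protocol or SAP. This stands too; the broken pointer alone would not be a finding. The mismatch between a one-reference method and two-reference hypotheses, and the gate itself, are choices that the article states.

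**Cost of the wider family.** Simply removing the gate keeps about 84% for combined versus sham, more than the 79.5% of the five-contrast family. That is true; the difference is the price of covering combined versus single.

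**Conclusion.** The point holds in a limited form. The gate is redundant for Dunnett's test and costs about 5 points of power for combined versus sham under the plan's own assumptions (about 84% to 78.6%), which puts that comparison below the 80% target. It makes the procedure conservative; it does not make a positive Dunnett result unsafe. Separately, no one-reference Dunnett set holds both the single-versus-sham comparisons and the combined-versus-single comparisons, and the interaction cannot fill the gap when effects are additive, as the power analysis assumes. The article does not support saying that a primary aim is untestable, or that the trial runs at 9% error. The figures rest on equal arms of 90, normal data and a common SD of 8.

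**What to change.** In the Statistical analyses section:

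1. Remove the omnibus condition for the Dunnett comparisons and keep the F test as descriptive.
2. Name double sham as the reference arm.
3. List combined vs CR and combined vs EX with the three sham comparisons, and cover all five in one stated procedure: max-t, or a closed or hierarchical one.
4. State where the interaction test of synergy sits in the error control, since it answers a primary aim.
5. Replace the pointer to a hypothesis section with the list itself.

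The change is about one paragraph and needs no more participants. With the max-t family, combined vs sham has 79.5% power under 4,2,2,0, against about 84% for ungated Dunnett and 78.6% as written. Each single vs sham falls from about 25% to 20%. Under 3,2,1,0 and 4,1,1,0, combined vs sham is about 1 point lower than as written (49.5% vs 50.4%, and 79.4% vs 80.7%). In return, every stated pairwise comparison has strong error control. Whichever procedure is chosen, power for a 2-point combined-versus-single difference stays low: 38.7% even unadjusted, with 252 per arm needed for 80%.

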	**Inclusion Criteria**
SDMT	1.282 SD or more below published normative data (10th percentile).

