### Randomization

Participants will be randomized to a treatment arm using block randomization by site. Block sizes will be blinded to study personnel and principal investigators. Randomization assignment will be conducted in REDCap (a secure web application for building and managing databases) within 24 h after the baseline assessment.

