### Outcomes and assessments

#### Primary outcome

The primary outcome of this study is the change in processing speed (PS) over the 12 weeks of training, assessed with the Symbol Digit Modalities Test (SDMT). The SDMT is available in several versions, and in the present study, 3 versions will be used in a randomized order to minimize practice effects when repeated [27]. There are several reasons why we chose PS as the primary outcome measure. First, it is well known that PS is the primary cognitive impairment in persons with MS [28] and as a primary cognitive construct, impaired PS itself can lead to problems in higher cognitive functioning such as executive abilities [29]. As such, improving PS may also improve other cognitive areas. Second, there is good preliminary data from smaller studies from multiple laboratories that both CR and exercise improve PS [24, 30–32]. Third, the existing RehaCom literature shows the most consistent and significant effect on PS [18, 33–36]. Fourth, a recent topical review of the SDMT found strong evidence supporting the reliability and validity of the test and recommended a responder definition of SDMT change approximating 4 points or 10% in magnitude [37]. Lastly, after an extensive review of potential cognitive outcome measures by the Multiple Sclerosis Outcome Assessment Consortium, the SDMT was recommended to the Federal regulators as *the* cognitive test of choice to be included in MS clinical trials [38].

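### The primary ANOVA of SDMT change leaves out site, the randomisation stratum, and baseline SDMT; adding both would give a modest gain in precision at no cost in data

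*Protocol article*

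**What the plan says.** All references are to the Protocol article.

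- **Endpoint** (Primary outcome): "the change in processing speed (PS) over the 12 weeks of training", measured with the SDMT.
- **Primary model** (Statistical analyses): "The primary analysis will utilize an ANOVA and include an interaction term for the combined treatments". No covariate is named for it.
- **Adjusted model** (Statistical analyses): "Additional analyses will be conducted as sensitivity analyses using Analysis of Covariance (ANCOVA"). Its covariates are described thus: "These will include site, gender, age and other covariates that may be seen to differ amongst the groups at baseline". Baseline SDMT is not on that list.
- **Allocation** (Randomization): "Participants will be randomized to a treatment arm using block randomization by site". There are 11 sites in six countries.
- **Eligibility** (Table 2): SDMT "1.282 SD or more below published normative data (10th percentile"). Table 5 places the pre-treatment SDMT at the in-person screening, so everyone randomised has one.
- **Secondary outcomes** (Statistical analyses): besides ANOVA and ANCOVA, "repeated measures mixed models will be used for measurements that are taken between baseline and 12 weeks". Table 5 and the Secondary outcome section also schedule these measures at 24 weeks.

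**The concern.** The text fixes the order of the two models, so this is a stated choice and not a detail left to an analysis plan. Three features of that choice deserve attention.

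First, blocking by site balances the arms within each site. If sites differ in mean change, an analysis without site keeps that variation in the error term although it no longer contributes to the differences between arms. The standard error is then too large and the test rejects too rarely.

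Second, a change score subtracts baseline with a coefficient fixed at 1. With the plan's own correlation of 0.80 and equal variances, the regression slope of follow-up on baseline is 0.80, so some predictable variation stays in the residual.

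Third, part of the sensitivity ANCOVA is open-ended: "other covariates that may be seen to differ amongst the groups at baseline". Observed imbalance after randomisation does not identify prognostic variables, and the final model cannot be known in advance.

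Precision is at stake in a trial with little to spare: power is 80.9% at the planned 90 per arm, and the Power analysis section itself gives 59% if the pattern of mean changes is 3, 2, 1, 0.

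**Working it through.** **Inputs from the Power analysis section.** Mean changes 4, 2, 2, 0; SD of change 8; n = 90 per arm; alpha 0.05; correlation between baseline and follow-up r = 0.80.

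**Step 1: the plan's own figure.** Non-centrality λ = n·Σ(mᵢ − m̄)²/SD² = 90 × 8/64 = 11.25, with 3 and 356 degrees of freedom. The non-central F gives power 0.80885, exactly as in Table 6. The other ten rows and the five sensitivity figures in the text also reproduce. The calculation is correct for an unadjusted ANOVA of change.

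**Step 2: add baseline, no truncation.** Write σ² for the cross-sectional variance, equal at both times.
- Variance of change: 2(1 − r)σ² = 0.40σ².
- Residual variance given baseline: (1 − r²)σ² = 0.36σ².
- Ratio: 0.36/0.40 = 0.90, so the residual SD is 8 × √0.90 = 7.59.
- λ = 11.25/0.90 = 12.5 and power is 0.852. It stays 0.852 if site is added and explains nothing, so the 10 degrees of freedom for site cost almost nothing.
- The planned power of 0.809 would need 82 per arm (328 in total) instead of 90 (360).

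**Step 3: add baseline, with the eligibility cut.** The share of the source population that passes the SDMT cut is not given. Assume 30-70%, with baseline a normal variable truncated from above. Its variance is then k = 0.26 to 0.49 of the full variance.
- Variance of change: (1 − r)²kσ² + (1 − r²)σ² = (0.04k + 0.36)σ².
- Ratio: 0.36/(0.36 + 0.04k) = 0.97 (k = 0.26) to 0.95 (k = 0.49).
- Power, keeping the SD of change at 8: 0.822 to 0.830.

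Eligibility uses scores adjusted for age, sex and education, so truncation of the raw score is only partial. The true ratio plausibly lies between Steps 2 and 3.

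**Step 4: add site as well.** The article gives no between-site variance. If site explains 3-5% of the variance of change (assumed), the residual ratio is multiplied by 0.97 to 0.95:
- low end: 0.97 × 0.97 = 0.941, power 0.834;
- high end: 0.90 × 0.95 = 0.855, power 0.871.

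**Step 5: error rate when site is left out.** Simulation with permuted blocks in 11 sites, 4,000 replicates per scenario and r = 0.80:

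| Site share (assumed) | Type I error, unadjusted | Power, unadjusted | Power, baseline + site |
|---|---|---|---|
| 0% | 0.049 | 0.80 | 0.85 |
| 5% | 0.043 | 0.82 | 0.87 |
| 10% | 0.034 | 0.81 | 0.89 |

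The unadjusted test moves below its nominal 5% level, not above it.

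**Step 6: the mixed-model sentence.** Read strictly, Table 5 has no secondary-outcome assessment visit lying between baseline and 12 weeks. Read as including both ends, the sentence still stops short of the 24-week assessment.

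**The case against.** The plan is coherent as it stands. Endpoint, model and sample size all rest on change, and Table 6 reproduces. Baseline is not ignored, because the change score subtracts it. Stable differences between sites in SDMT level cancel in a change score as well; only differences in change matter. A site-adjusted model is already planned as sensitivity, and with the eligibility cut the gain from baseline alone is only 1.3 to 2.2 percentage points of power. All of this stands, and it limits the point to efficiency and calibration.

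Some stronger readings are tempting, and the article does not support them:

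- *Selection on low SDMT biases the comparison through regression to the mean.* All arms pass the same cut before randomisation, so the effect is equal across arms in expectation. The cut in fact reduces what baseline adjustment can gain.
- *Truncation lowers the correlation, so the gain is large.* The in-sample correlation would indeed fall to about 0.57-0.68. But the shortcut ratio (1 + r)/2 needs equal variances at both times, which truncation breaks. Step 3 gives the proper ratio.
- *The ANCOVA is chosen by observed imbalance.* Site, gender and age are named in advance. Only the remaining covariates are open, and only in a sensitivity model, so the primary test is untouched.
- *Dropout is left unaddressed.* Multiple imputation and informative-censoring scenarios are planned as sensitivity analyses of the primary result.
- *No 24-week outcome has a longitudinal model.* The MRI section gives DTI and functional-connectivity measures such models, and MRI is acquired at 24 weeks.

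**Conclusion.** The point holds as one of efficiency and pre-specification. The primary ANOVA omits the factor by which randomisation is blocked and does not use baseline SDMT as a covariate. It remains unbiased, the sample size is not wrong, and any error in the significance level is on the conservative side.

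Against 80.9% as planned, power would be about 82-83% with baseline under the assumed truncation, at most 85% at r = 0.80 without it, and about 83-87% with an assumed 3-5% of variance due to site. The truncation and site figures are assumptions; the correlation, SD and effect pattern are the plan's own. The gain is modest, but it needs no further patients or measurements. The wording of the mixed-model sentence is a lesser, separate matter that concerns only the non-MRI secondary outcomes.

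**What to change.** 1. Make the primary model an ANCOVA of 12-week SDMT (or its change) on CR, EX, CR × EX, baseline SDMT and site, with age and sex fixed in advance as covariates. State that the in-person screening SDMT serves as baseline.
2. Keep the unadjusted ANOVA of change as a sensitivity analysis.
3. In the sensitivity ANCOVA, replace the open-ended covariates with a list fixed in advance, chosen for expected prognostic value and not by tests of baseline differences.
4. Reword the mixed-model sentence so that the models for the non-MRI secondary outcomes cover the baseline, 12-week and 24-week visits.

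The cost is wording only. All the variables are already collected, and the sample size can stay as it is. The change should be made before the data are unblinded.

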**Methods:**

This study is a multisite, randomized, double-blinded, sham controlled clinical trial of CR and aerobic exercise. Three hundred and sixty subjects from 11 sites will be randomly assigned into one of four groups: CR plus aerobic exercise; CR plus sham exercise; CR sham plus aerobic exercise and CR sham plus sham exercise. Subjects will participate in the assigned treatments for 12 weeks, twice a week.

All subjects will have a cognitive and physical assessment at baseline, 12 weeks and 24 weeks. In an embedded sub-study, approximately 30% of subjects will undergo structural and functional MRI to investigate the neural mechanisms underlying the behavioral response. The primary outcome is the Symbol Digit Modalities Test (SDMT) measuring PS. Secondary outcome measures include: indices of verbal and non-verbal memory, depression, walking speed and a dual cognitive-motor task and MRI.

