#### Secondary outcome

All secondary outcomes will be assessed during the in-person interview or the baseline assessment, at the post 12-week assessment and at the 24-week follow-up assessment.

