**Customized**							
Phone Interview	X						
Consent form		X					
Medication list		X			X		X
Goal Setting Sheet				X			
Adverse Event form*****				X			
Post Intervention Interview						X	
Post Intervention Survey							X
Serious Adverse Event form*****							X

*Available in three parallel versions;** measured during the week following the intervention; ***only performed at 3 sites; **** AHA/ACSM Health/Fitness Facility Pre participation Screening Questionnaire *****only completed if necessary

Abbreviations: *BICAMS* Brief International Cognitive Assessment for MS, *SDMT* Symbol Digit Modalities Test, *CVLT* California Verbal Learning Test, *BVMT-R* Brief Visuospatial Memory Test-Revised, *WTAR* Wechsler Test of Adult Reading, *NART* National Adult Reading Test, *CMI* Cognitive-Motor Interference, *6MWT* Six Minute Walk Test, *IET* Incremental Exercise Test, *Functional MRI* Functional Magnetic Resonance Imaging, *GLTEQ* Godin Leisure-Time Exercise Questionnaire, *BDI-II* Beck Depression Inventory-II, *FAMS* Functional Assessment of Multiple Sclerosis, *EQ-5D-5L* European Quality of Life-5 Dimensions, *MSIS-29 V2* Multiple Sclerosis Impact Scale-29 Items Version2, *MSWS-12* Multiple Sclerosis Walking Scale 12 Items, *PDQ-20* Perceived Deficits Questionnaire 20 Items, *MFIS* Modified Fatigue Impact Scale, *HADS* Hospital Anxiety and Depression Scale

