Physical activity will be determined by accelerometry. Participants will wear the accelerometer (Actigraph; http://actigraphcorp.com/) on an elastic belt around the waist located above the non-dominant hip during the waking hours for 7 days before the first intervention week and during the week following completion of the intervention. This method has proven reliable in people with MS [53]. It will provide data on the degree of lifestyle physical activity (i.e. steps/day and minutes/day of moderate to vigorous physical activity) immediately before and after the intervention phase.

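### The repeated measures mixed model is tied to an interval with no efficacy visit inside it, so the 24-week clinical outcomes fall outside the model

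*Protocol article*

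**What the plan says.** All references are to the protocol article.

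- **Method for secondary outcomes** (Statistical analyses): "Secondary outcomes will be similarly assessed using ANOVA and ANCOVA procedures", and in addition "repeated measures mixed models will be used for measurements that are taken between baseline and 12 weeks".
- **Timing of secondary outcomes** (Secondary outcome): at in-person screening or baseline, then "at the post 12-week assessment and at the 24-week follow-up assessment".
- **Who is followed** (Abstract, Methods): "All subjects will have a cognitive and physical assessment at baseline, 12 weeks and 24 weeks".
- **Default data set** (Statistical analyses): "All analyses will be based on available data, unless otherwise stated, and the intent-to-treat principle". Multiple imputation is described there as a sensitivity analysis of the primary results.
- **Primary outcome**: "change in processing speed (PS) over the 12 weeks of training", measured with the SDMT and analysed by ANOVA with an interaction term, an overall test and then Dunnett comparisons.
- **Accelerometry** (Physical performance): worn "7 days before the first intervention week and during the week following completion of the intervention". The Table 5 footnote to its mark in the intervention column agrees: "measured during the week following the intervention".

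**The concern.** The article names a repeated measures model and gives it a scope, but the scope does not match the visit schedule. The repeated post-baseline visits are at 12 and 24 weeks, and the sentence stops at 12. An analysis plan that followed it would have almost nothing to fit. One that departed from it would contradict the published protocol.

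The 24-week comparison of the arms is what is at stake. Under ANOVA or ANCOVA on whoever attends at 24 weeks, a participant seen at 12 weeks but not at 24 contributes nothing to the 24-week estimate. If those who leave did worse at 12 weeks, and this happens more in one arm than another, the 24-week arm difference is biased. The 12-week values that would correct it have been collected but are not used.

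**Working it through.** **1. Is there an efficacy outcome between baseline and 12 weeks?** The 12-week intervention column of Table 5 has three entries.

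| Entry | Efficacy outcome inside the interval? |
|---|---|
| Goal setting sheet | No, an intervention tool |
| Adverse event form | No, safety |
| ActiGraph | No, the footnote and the Physical performance text place it in the week after the intervention |

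The count is 0. If both ends are included, the model has two time points, baseline and 12 weeks. The 24-week visit is outside it on either reading.

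**2. What is repeated at 24 weeks?** In Table 5: SDMT, CVLT, BVMT-R, cognitive-motor interference, 6-minute walk, incremental exercise test, FAMS, EQ-5D-5L, MSIS-29, MSWS-12, PDQ-20, MFIS, HADS and MRI. Accelerometry is not repeated. The MRI substudy has its own longitudinal models for DTI and functional connectivity measures, in about one third of participants. The other outcomes in this list have only the ANOVA and ANCOVA sentence.

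**3. Is the planning figure affected?** It reproduces and is not in question. The noncentrality is n × Σ(mᵢ − m̄)² / SD². With means 4, 2, 2, 0 the sum of squares is 4 + 0 + 0 + 4 = 8, so 90 × 8 / 64 = 11.25. With 3 and 356 degrees of freedom and alpha 0.05 the power is 0.80885, as in Table 6. All 11 rows match.

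**4. Illustration of the bias at 24 weeks.** The inputs are:

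- SD of change 8 (Power analysis).
- Correlation between any two SDMT scores ρ = 0.80. The Power analysis gives this for test and retest; applying it to all three pairs of visits is an assumption.
- 10% or 20% lost after week 12 in one arm, with loss in the comparison arm unrelated to outcome. This is an assumption, because the article gives no rate.

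With equal variances σ², each change from baseline has variance 2σ²(1 − ρ), and the two changes have covariance σ²(ρ − ρ − ρ + 1) = σ²(1 − ρ). Their correlation is therefore r = 0.5.

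The bias of the 24-week arm mean among those who stay is 8 × r × E(z | stays), where z is the standardised 12-week change.

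- *Extreme case: the worst fraction q all leave.* E(z | stays) = φ(z_q)/(1 − q).
  - q = 10%: 0.1755/0.90 = 0.195, so the bias is 8 × 0.5 × 0.195 = 0.78.
  - q = 20%: 0.2800/0.80 = 0.350, so the bias is 8 × 0.5 × 0.350 = 1.40.
- *Graded case: the odds of leaving are about halved per SD better 12-week change.* By numerical integration:
  - 10% lost: E(z | stays) = 0.067, so the bias is 8 × 0.5 × 0.067 = 0.27.
  - 20% lost: E(z | stays) = 0.130, so the bias is 8 × 0.5 × 0.130 = 0.52.

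With the graded mechanism, loss of 10–30% and r from 0.5 to 0.8, simulation gave 0.28 to 1.23 points. An analysis that also used the 12-week value had a bias of 0.02 or less in absolute size.

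**5. Precision.** If loss is completely at random there is no bias. The variance of the arm mean using the 12-week value is then 1 − r²d times the available-case variance, where d is the fraction lost. For r = 0.5 and d = 10% this is 0.975. For r = 0.8 and d = 30% it is 0.808.

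**The case against.** The strongest reply is that this is a slip in one clause of a condensed article, and that the modelling of 24-week data belongs in the analysis plan. The clause may well be a slip. But it states a scope that conflicts with the article's own schedule, which is different from leaving a detail out.

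Other points limit what can be claimed, and they stand:

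- A reader might infer that the model applies to nothing. Attendance, intensity, duration, heart rate and perceived exertion are recorded during training. They are monitoring data rather than listed outcomes, but they are measurements, and an inclusive reading also gives the baseline and 12-week pair.
- A reader might infer that the whole second follow-up lacks a longitudinal model, or that every outcome is repeated then. MRI measures have their own models, and accelerometry is not repeated.
- Available-case analysis at 24 weeks is inferred from the general default and from imputation being named only for the primary results. It is not stated for that visit, and the word *similarly* could be read to carry imputation over to secondary outcomes.
- A reader might infer that ANOVA cannot test whether the arm difference changes from 12 to 24 weeks. An ANOVA of the 24-minus-12-week difference would do so, though only in people with both visits.
- The 0.8–1.4 point figures are close to a worst case. If arms lose similar people at similar rates, the bias largely cancels. The likelihood analysis removes it in the simulation because dropout was made to depend only on the observed 12-week value.
- The illustration is in SDMT points, whereas the clause governs secondary outcomes.

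**Conclusion.** The stated scope of the mixed model conflicts with the visit schedule and should be corrected. As written, the clinical outcomes repeated at 24 weeks fall to ANOVA and ANCOVA, by default on available data, and the 12-week values of people who miss 24 weeks go unused.

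The possible bias is about 0.3–0.5 SDMT points under graded dropout and 0.8–1.4 in the extreme case. For scale, the Power analysis assumes 2 points for each single intervention, at 12 weeks. These figures rest on assumed loss of 10–20% in one arm related to the 12-week result, unrelated loss in the other, a change SD of 8 and a correlation of 0.5 between changes. They illustrate the risk and do not predict it.

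Nothing here touches the primary 12-week SDMT analysis or its power, and the documents give no reason to replace that analysis with a mixed model.

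**What to change.** Leave the primary 12-week SDMT ANOVA unchanged, with its interaction term, overall test and Dunnett comparisons. Replace the mixed-model clause with wording such as:

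*Outcomes measured at baseline, 12 and 24 weeks will be analysed with a repeated measures mixed model for the 12- and 24-week values, with arm, visit, arm-by-visit, baseline value and site, and an unstructured covariance. Arm contrasts will be reported at 12 and at 24 weeks. For the SDMT this model is supportive.*

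For the SDMT, the baseline value is the one taken at in-person screening, where Table 5 places it. Accelerometry, with one post-intervention measurement, stays under ANCOVA. State also whether multiple imputation extends to the 24-week results.

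The cost is one revised sentence and a little more analysis code, with no new data. The model relies on dropout being explained by observed values, so a sensitivity analysis for dropout is still needed.
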